# Transcutaneous electrical acupoint stimulation for high-normal blood pressure: study protocol for a randomized controlled pilot trial

**DOI:** 10.1186/s13063-021-05039-5

**Published:** 2021-02-15

**Keywords:** Transcutaneous electrical acupoint stimulation, High-normal blood pressure, Lifestyle interventions, Prehypertension

## Abstract

**Background:**

High-normal blood pressure (BP) is associated with increased all-cause, cardiovascular mortality and frequently progresses to hypertension. Transcutaneous electrical acupoint stimulation (TEAS) might be a non-pharmaceutical therapy option to control BP. This trial aims to determine the effectiveness and safety of TEAS combined with lifestyle modification for high-normal BP.

**Methods/design:**

This prospective, randomized, and parallel clinical trial will be conducted in a community service center in China. Sixty participants with high-normal BP will be randomly allocated to receive TEAS plus lifestyle modification (intervention group) or lifestyle modification alone (control group) in a 1:1 ratio. In addition to lifestyle modification, the intervention group will receive TEAS at four acupoints for 30 min, 4 times weekly for 12 weeks for a total of 48 sessions at home. The control group will receive same lifestyle modification but no TEAS. The primary outcome will be the change in mean systolic blood pressure at 12 weeks from the baseline measurement. Secondary outcomes include the change of mean diastolic blood pressure, proportion of subjects with progression to hypertension, quality of life, body mass index, and waist circumference. Adverse events during the trial will be monitored.

**Discussion:**

This trial will explore the feasibility and provide potential evidence for the effectiveness and safety of TEAS plus lifestyle modification for high-normal BP. Furthermore, this pilot trial is being undertaken to determine the feasibility of a full scale definitive randomized controlled trial. The results of this study will be published in a peer-reviewed journal.

**Trial registration:**

Chinese Clinical Trial Registry, ChiCTR 1900024982. Registered on August 6, 2019.

**Supplementary Information:**

The online version contains supplementary material available at 10.1186/s13063-021-05039-5.

## Background

Increased blood pressure (BP) is a leading modifiable risk factor for global disease burden and premature mortality [1, 2]; even mild BP elevations manifesting as “prehypertension or high-normal BP” have been associated with increased all-cause mortality [3]. High-normal BP elevates the risk of higher morbidity and mortality from cardiovascular disease (CVD) and stroke [4, 5], as well as increasing the risk of incident end-stage renal disease [6]. High-normal BP frequently progresses to hypertension [7], and affects approximately 41.3% (estimated 435.3 million) of adults in China according to the Chinese guideline [8]. High-normal BP may be a window of opportunity to prevent hypertension and its cardiovascular consequences [9]. The 2018 Chinese Guidelines for Prevention and Treatment of Hypertension defined high-normal BP as systolic blood pressure (SDP) of 120–139 mmHg and/or diastolic blood pressure (DBP) of 80–89 mmHg [10]. However, the 2017 American College of Cardiology (ACC)/American Heart Association (AHA) BP guideline defined stage 1 hypertension as SBP of 130–139 mmHg or DBP of 80–89 mmHg [11]. Therefore, a large number of individuals who had prehypertension or high-normal BP before are now considered to have hypertension according to the new American guideline.

Data are lacking as to how this range of BP should be managed and most guidelines do not recommend pharmacological interventions for high-normal BP without cardiovascular comorbidity [7]. Long-term medication is costly to control BP particularly in developing nations, for instance, the price in China was 3.3 times the price in the USA on average [12]. Despite limited effectiveness, virtually, all guideline statements recommend and encourage lifestyle interventions to prevent hypertension [7]. However, lifestyle modification is a dynamic process and requires long-term persistence [13], and the challenges of lifestyle changes extend beyond counseling for physicians and patient adherence [14]. For the majority of US adults with a SBP of 130–139 or DBP of 80–89 mmHg, non-pharmaceutical therapy by itself is the recommended treatment [15].

Acupuncture as a non-pharmaceutical therapy is widely used in the treatment of hypertension [16], and some evidence suggests potential effectiveness [17]. Transcutaneous electric acupoint stimulation (TEAS), a noninvasiveness therapy similar to acupuncture, is used as a clinical alternative to electrical acupuncture and manual acupuncture [18]. It is considered a combination of transcutaneous electrical nerve stimulation and acupuncture. Transcutaneous electrical stimulation therapy has the advantages of being easy to use, which is more “user friendly” requiring minimal training for physicians and patients, and if convenient for clinical application [19]. Two trials have explored the efficacy of simple transcutaneous electrical nerve stimulation based interventions for adults with or without hypertension to reduce blood pressure [20, 21]. And choosing acupoints with antihypertensive effect based on traditional Chinese medicine theory for stimulation may increase the effect of transcutaneous electrical nerve stimulation. Previous studies have shown that TEAS has effects on the nervous system that include regulation autonomic nervous system function and enhancement of the activity of the vagus nerve, thereby potentially affecting BP [22]. This approach was supported by the studies of Jacobsson et al. [23] and Zhang et al. [24] using the Hans electrical stimulator treating acupoints on the forearm showed significant reduction in blood pressure. However, studies of TEAS for high-normal BP are lacking. The main objective of this preliminary trial is to assess the effectiveness and safety of TEAS combined with lifestyle modification in participants with high-normal BP, to calculate the sample size for a future efficacy study.

## Methods

### Study design

This prospective, randomized, and parallel design clinical trial of high normal BP participants will be conducted in a large public-sector clinic in Beijing, China. The trial protocol was approved and reviewed by the Ethics Committee of Beijing University of Chinese Medicine and will be reported based on SPIRIT guidelines. The corresponding author will be responsible for trial scientific oversight. The study was registered on Chinese Clinical Trial Registry (ChiCTR 1,900,024,982) on August 6, 2019.

### Study population

The study population will be comprised of individuals with high-normal BP (2018 Chinese Guidelines for Prevention and Treatment of Hypertension [10]) at a community service center (Nanyuan community health service centers in Beijing, China). Study investigators will be responsible for recruiting and gaining informed consent. All participants will provide written informed consent before enrollment and randomization at the outpatient department.

#### Inclusion criteria

Aged between 35 and 65 years (either gender)SBP of 120–140 mmHg and/or DBP of 80–90 mmHg on at least 2 separate visitsNo language disorder or mental retardation, so that participants will be able to answer and complete the questionnaire completelyWilling to sign written informed consent

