### Outcomes

#### Primary outcome

The primary outcome will be the change in mean SBP from baseline to 12 weeks.

BP will be measured as proposed by the 2018 Chinese Guidelines for Prevention and Treatment of Hypertension [10]. Participants will be asked to avoid exercise, alcohol, cigarettes, and coffee/tea for at least 30 min before the BP measurement. BP will be measured with the participant in a seated position after 5 min of quiet rest. Participants will be required to take blood pressure measurement. A digital BP monitor (HEM-7136, OMRON Corporation, Kyoto, Japan) with suitable cuff size will be used. Clinicians will record three sequential BP readings at 5-min intervals, and the final BP will be calculated by removing the initial reading and calculating the mean from the two remaining readings.

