##### Proportion of progression to hypertension

The proportion of subjects with hypertension (BP > 140/90 mmHg) will be calculated among the high-normal BP participants at 12, 24, and 36 weeks.

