### Statistical methods

#### Sample size

This pilot study aims to assess the effectiveness and safety of TEAS combined with lifestyle modification for high-normal BP and determine the feasibility of a further large clinical trial. The minimum sample size for exploratory trials is 20 to 30 per group according to Provisions for Drug Registration in China. It is generally accepted that at least 30 participants are required for a pilot study [33]. We selected the maximum of 30 participants, and the sample size of 60 participants was determined. The results of this study will facilitate the calculation of an appropriate sample size for further randomized clinical trials.

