#### Statistical analysis

Analysis will be carried out on an intention-to-treat (ITT) basis and will be performed using SPSS 23.0 statistical software (IBM SPSS Statistics, New York, USA) with a 2-sided *P* value of less than 0.05 considered significant. The measurement of data that conforms to the normal distribution will be expressed as mean ± SD, the measurement data that does not conform to a normal distribution will be expressed by the median (interquartile range), and counting data will be represented by cases (percentages). The continuous variables will be evaluated by using a *t* test or the Mann-Whitney *U* test for comparison. The chi-square test or Fisher’s exact test will be employed to compare binary variables. Missing data will be imputed using the last observation carried forward.

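### The entry range and the hypertension cut-off do not match the high-normal range the protocol cites, so the progression outcome is loosely defined at its limits and at baseline

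*Protocol article*

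**What the plan says.** Four places in the protocol article bear on the point.

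- Background: the 2018 Chinese guideline "defined high-normal BP as systolic blood pressure (SDP) of 120–139 mmHg and/or diastolic blood pressure (DBP) of 80–89 mmHg". Study population ties the participants to high-normal BP under that same guideline.
- Inclusion criteria: "SBP of 120–140 mmHg and/or DBP of 80–90 mmHg", found at two or more separate visits.
- Exclusion criteria: secondary hypertension, and drugs affecting BP within the previous 2 months. Untreated primary hypertension is not listed.
- Secondary outcomes, under the progression heading: "The proportion of subjects with hypertension (BP > 140/90 mmHg) will be calculated among the high-normal BP participants at 12, 24, and 36 weeks".

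The BP value itself comes from three readings, by "removing the initial reading and calculating the mean from the two remaining readings" (Primary outcome), so it can fall on half-millimetres.

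**The concern.** Progression should mean a move from not hypertensive to hypertensive. That needs an entry range and an event threshold that meet without a gap or an overlap, and a stated rule for combining the two components. Here the entry range ends 1 mmHg above the cited range on each component, the event needs a strict excess over 140/90, and the component rule is left open.

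The proportion progressing is named in the Abstract as a secondary outcome and is assessed at three time points. The pilot is also meant to inform a larger trial. An event rate that depends on how the rule is read would carry into that planning, and an open definition can be settled after the data have been seen.

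**Working it through.** **1. The limits side by side**

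| Source | SBP | DBP | Combination |
|---|---|---|---|
| Cited range (Background) | 120–139 | 80–89 | and/or |
| Inclusion criteria | 120–140 | 80–90 | and/or |
| Progression outcome | > 140 | > 90 | not stated |

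The upper limits differ by 140 − 139 = 1 mmHg and 90 − 89 = 1 mmHg.

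**2. Test values**

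| BP | A component above the cited range? | Eligible, read literally? | Event, either component | Event, both components |
|---|---|---|---|---|
| 138/84 | no | yes | no | no |
| 140/85 | yes (SBP) | yes | no | no |
| 135/95 | yes (DBP) | yes | yes | no |
| 150/85 | yes (SBP) | yes | yes | no |

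The two readings of the event fail differently. Under the either-component reading, 135/95 or 150/85 at entry already meets the outcome. Under the both-components reading nobody eligible can meet it at entry, because eligibility needs at least one component at or below its limit. That reading, however, misses a rise in one component alone.

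**3. Illustrative size**

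The documents give no means, SDs or correlation for BP, so everything here is assumed. SBP and DBP are bivariate normal with correlation 0.6. Each value is the mean of two integer readings with within-visit SD 4 (SBP) and 3 (DBP). There are 2,000,000 draws per scenario. One visit is simulated, not two.

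| Mean (SD) SBP; DBP | A: exactly 140 or 90, both capped | A × 60 | B: > 140 or > 90, uncapped | C1: ≥ 140 or ≥ 90 | C2: > 140 or > 90 | C3: > 140 and > 90 |
|---|---|---|---|---|---|---|
| 125 (12); 80 (8) | 2.5% | 1.5 | 16.7% | 18.9% | 17.5% | 4.1% |
| 128 (12); 82 (8) | 3.1% | 1.8 | 21.7% | 26.8% | 25.0% | 6.9% |
| 130 (10); 83 (7) | 3.2% | 1.9 | 21.1% | 27.4% | 25.4% | 6.9% |
| 132 (10); 84 (7) | 3.7% | 2.2 | 24.8% | 33.6% | 31.3% | 9.6% |
| 130 (15); 82 (10) | 3.3% | 2.0 | 28.2% | 36.1% | 34.5% | 11.6% |

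A and B are shares of eligible people. C1 to C3 apply each event rule to the whole assumed distribution.

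- Boundary alone: A is about 1.5 to 2.2 of 60. C1 − C2 runs from 18.9 − 17.5 = 1.4 to 33.6 − 31.3 = 2.3 percentage points. At 2 points that is 0.02 × 30 = 0.6 participants per arm.
- Uncapped criterion: B corresponds to 0.167 × 60 = 10 up to 0.282 × 60 = 17 participants who would meet the either-component event at entry.
- Component rule: C2/C3 runs from 34.5/11.6 = 3.0 to 17.5/4.1 = 4.3.
- One participant moves an arm's proportion by 1/30 = 3.3 points.

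**The case against.** The case on the other side is substantial.

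- The inclusion criterion and the outcome agree with each other at the boundary: 140 or 90 is eligible and is not an event. The 1 mmHg mismatch alone cannot make someone an event at entry. This stands.
- The cited definition carries the same and/or, so on that feature the criterion follows its source. Study population and the outcome section both speak of high-normal participants, which suggests that 150/85 was never meant to qualify. This stands as evidence of intent. An eligibility rule is applied person by person, though, and no cap is written down.
- A slash threshold is normally read as a limit on each component, so the both-components reading is the less natural one. That too stands. The three- to four-fold gap shows why the rule should be stated, not what the trial will find.
- The sizes rest on assumed distributions and ignore the two-visit requirement. They are illustrations only.
- The same rule applies to both arms, and no bias between arms has been shown.

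A reader might infer that the cut-off directly contradicts the guideline. The article does not report the guideline's hypertension threshold; the conflict is inferred from a high-normal range that ends at 139/89. A reader might also infer that many hypertensive people were enrolled. Nothing in the document shows that, and a sensible cap may have been used in practice.

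**Conclusion.** The point holds as a definitional fault in a secondary outcome and should be fixed. The mismatch between the cited range and the entry range is on the page. So are the missing cap and the missing component rule.

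Its certain part is small: about 2 percentage points, or roughly 2 of 60, under the assumed distributions. Its larger part is conditional. It needs the criterion to have been applied without a cap (about 17–28% of eligible people already above a limit, on the same assumptions) or the event to be read as requiring both components.

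It would go too far to say that the primary result is compromised. The primary outcome is the change in mean SBP at 12 weeks, its calculation uses no cut-off, and the issue reaches it only through who was enrolled.

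**What to change.** 1. Reconcile Background, Inclusion criteria and the progression outcome so that they use one set of limits.
2. For analysis, define progression as leaving the protocol's own cited range upward on either component: SBP ≥ 140 and/or DBP ≥ 90 mmHg. Apply this to the unrounded two-reading mean, so that 139.5 counts as below the limit. This aligns the outcome with the range the protocol cites; it is not a view on clinical thresholds.
3. Compute the proportion only among participants with baseline SBP < 140 and DBP < 90 mmHg.
4. Trial status reports all 60 randomised, so do not rewrite eligibility retrospectively. State the rule actually applied, including whether the other component was capped. Report by arm how many had baseline BP outside 120–139/80–89, showing separately those at or above 140 or 90 on either component.
5. Optionally, repeat the primary analysis without those participants.

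Date the definition and settle it before outcomes are compared by arm; if that has already happened, say so. The cost is wording and recoding of BP values already collected. The downside is a smaller denominator for progression: few participants are lost if a cap was applied in practice, more if it was not.

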#### Exclusion criteria

Contraindications for the use of electrostimulation such as use of a cardiac pacemaker or other implanted medical devices; suffering from acute diseases, infectious diseases, malignant tumors, cardiovascular disease, cerebrovascular disease, liver and kidney dysfunction, or other malignant diseases; dermatological abnormalities on the skin of the acupuncture pointsSecondary hypertensionReceived antihypertensive drugs or other drugs that affect BP in the previous 2 monthsUncontrolled diabetesReceived acupuncture treatment in the previous 1 monthDrug or alcohol abusePregnant, lactating, or planning pregnancy during the trialParticipated in another research trial

### Randomization and allocation concealment

Eligible participants will be randomized into one of two groups: the intervention group or the control group (1:1), using block random method and the block size is 6. The randomization sequence will be prepared by a professional statistician ([name]) with the SAS9.3 software, who is not involved in assessment, treatment, or analysis of the study, to ensure balance in baseline BP across the groups. When an eligible participant needed to receive a random group, the random number and the group assignment will be sent from the random number administrator to the recruiter via phone or short message.

The participants and study staff interacting with participants will not be blinded to group assignment in the trial. The outcome assessors and trial statisticians, who will not be involved in the intervention, will be blinded.

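### Blocks of 6 with no stated BP stratum balance group size only, not baseline BP as the article claims, and the stated primary comparison does not adjust for baseline SBP

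*Protocol article*

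**What the plan says.** The Protocol article, section Randomization and allocation concealment, describes 1:1 allocation "using block random method and the block size is 6". A statistician independent of assessment, treatment and analysis prepares the list, and the sentence ends with the purpose "to ensure balance in baseline BP across the groups". No stratification factor, BP category or minimisation is named.

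The same section says that for each eligible participant "the random number and the group assignment will be sent from the random number administrator to the recruiter via phone or short message". It adds: "The participants and study staff interacting with participants will not be blinded to group assignment in the trial". Outcome assessors and trial statisticians are to be blinded. Under Study population, "Study investigators will be responsible for recruiting and gaining informed consent". The abstract says the trial "will be conducted in a community service center in China".

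The primary outcome is change in mean SBP from baseline to 12 weeks. The Statistical analysis section compares continuous variables by t test or Mann-Whitney U test and mentions no covariate. Trial status reports that all 60 participants have been randomised.

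**The concern.** The property claimed does not follow from the method described. Permuted blocks keep the arm counts close as recruitment proceeds. They say nothing about which BP values fall in which arm unless blocks are formed within BP strata. The independence of the statistician, to which the purpose clause could also attach, does not balance BP either.

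This matters because the primary outcome is a change in the variable said to be balanced. A change score does not remove a baseline difference: through regression to the mean, the arm that starts higher tends to fall more, whatever the treatment does. A reader who accepts that baseline BP balance is assured will put more trust in the unadjusted comparison than the design earns, and the estimate is meant to inform the definitive trial.

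There is a second, lesser issue. One fixed block size, in an open single-centre trial where assignments go to the recruiter one by one, leaves room for later allocations in a block to be deduced from earlier ones.

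**Working it through.** The article gives no figure for imbalance or predictability, so there is none to reproduce.

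**Inputs.** N = 60, 30 per arm (Sample size); 1:1 blocks of 6, hence 60/6 = 10 full blocks (Randomization); SBP 120–140 mmHg and/or DBP 80–90 mmHg (Inclusion criteria). The baseline SBP SD is not given. I assume 4 to 8 mmHg; a uniform spread over 120–140 would give 20/√12 = 5.8.

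**1. Chance imbalance in baseline SBP.**
- SE of the difference in means = SD × √(1/30 + 1/30) = SD × √(2/30) = 0.258 SD.
- P(|difference| > 0.25 SD) = P(|Z| > 0.25/0.258) = 0.33.
- P(|difference| > 0.5 SD) = P(|Z| > 0.5/0.258) = 0.053.

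| Assumed SD (mmHg) | 95% chance range (mmHg) | P(difference beyond 2 mmHg) |
|---|---|---|
| 4 | ±2.0 | 5% |
| 5 | ±2.5 | 12% |
| 5.8 | ±2.9 | 18% |
| 6 | ±3.0 | 20% |
| 8 | ±4.1 | 33% |

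**2. Does blocking help?** By simulation at SD 5, the SD of the baseline difference is 1.28 mmHg with blocks of 6 and 1.30 mmHg with an unblocked 30/30 split, so blocking does essentially nothing for BP. Blocks of 6 within two strata split at the median give 0.81 mmHg.

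**3. Effect on the stated comparison.** With equal SDs at both visits and baseline–follow-up correlation r, a baseline difference d shifts the unadjusted difference in change by (1 − r) × d in size. With r = 0.5 (an assumption) and d = 2 mmHg, that is 0.5 × 2 = 1 mmHg. Over r = 0.3 to 0.7 it is 1.4 to 0.6 mmHg. ANCOVA removes this shift. Its error variance relative to the change score is (1 − r²)/[2(1 − r)] = (1 + r)/2, which is 0.75 at r = 0.5 (0.65 to 0.85 over the same range).

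**4. Predictability of fixed blocks.** A 3:3 block has C(6,3) = 20 orderings. An allocation is certain once one arm is full.
- The run of certain allocations has length 1 in 12 orderings, 2 in 6 and 3 in 2.
- Mean = (12×1 + 6×2 + 2×3)/20 = 30/20 = 1.5 per block. The closed form 2m/(m+1) with m = 3 agrees.
- Share = 1.5/6 = 25%. Over 10 blocks that is 15 of 60 on average, never fewer than 10, with a simulated 95% range of 11 to 19.
- Always guessing the less-filled arm is right 3 + (64/20 − 1)/2 = 4.1 times in 6, or 68%, against 50% by chance.

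**5. Varied block sizes, recruiter knowing only the set of sizes (simulation).** Certain allocations fall to about 6% (sizes 4, 6) or 2% (sizes 4, 6, 8). Best-guess accuracy stays at about 69% and 68%.

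**The case against.** The case on the other side is substantial.

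- **Chance imbalance is ordinary.** The 33% and 5% apply to any unstratified 30/30 trial, and the t test's error rate already allows for them. This stands: the figures do not show an invalid test or a failure of concealment. They show that balance is not assured and that a given trial's estimate can be shifted.
- **Covariates are commonly left to the SAP.** True, and silence alone would be no finding. But the article does name its comparison, that comparison does not use baseline as a covariate, and the same article claims a balance the design lacks. Improving a stated choice is fair comment.
- **The article is condensed.** Absence of stratification is read from silence. If the full protocol stratified by BP, the fault becomes one of reporting, and the strata should be stated and used in the analysis.
- **The 25% is an upper bound.** It needs a recruiter who knew the size and followed the whole sequence. Investigators, in the plural, recruit; if they did not pool assignments, the figure falls. The article was published on 15 February 2021, after all 60 had been randomised, so the printed text could not have told them the size. Independent preparation of the list, remote release, consent before randomisation and BP qualifying on at least two visits all limit manipulation. This stands, and the point is only a caution.

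A reader might infer that a quarter of allocations were in fact foreseen, that the recruiter also decided eligibility, or that the balance claim is why baseline was left out of the tests. The documents support none of these. They do not say who judged eligibility or who knew the block size, and the analysis section never refers to the balance claim.

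**Conclusion.** The claim of BP balance is wrong for the method described. The expected chance difference in baseline SBP has an SE of 0.258 SD: it exceeds 0.25 SD in about a third of such trials and 0.5 SD in about one in twenty. In mmHg the 95% range is ±2.0 to ±4.1 for assumed SDs of 4 to 8. The stated t test or Mann-Whitney comparison on change in SBP leaves part of any such difference in the estimate, about 1 mmHg for a 2 mmHg imbalance at an assumed correlation of 0.5. These figures rest on a normal approximation and on there being no stratification beyond what the article states.

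Predictability is secondary and conditional: at most 25% of allocations certain in expectation, for a recruiter with full knowledge of size and sequence. Nothing shows that this happened. The point deserves correction but does not threaten the trial's validity.

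**What to change.** - **Wording.** Delete the claim of BP balance, or say that blocking balances group size only. If the full protocol stratified by BP, state the strata and include them in the analysis.
- **Analysis.** Make the primary analysis an ANCOVA of 12-week SBP (or of the change) with baseline SBP as covariate. The data are already collected and SPSS fits the model; there is no cost beyond fixing the change before the outcome data are analysed.
- **Optional check.** Since all 60 are randomised, the allocation cannot be changed. Baseline SBP can be described against the probability of TEAS implied by earlier allocations in the block. This takes one table from the existing list. With about 15 certain allocations, roughly 7 or 8 per arm, it has low power, so a null result should not be read as reassurance.
- **Definitive trial.** Vary the block sizes at random and withhold them from recruiters, at the price of slightly looser group-size balance. This cuts certain knowledge from 25% to about 2–6% but hardly changes best-guess accuracy, and the plan should say so. If balance in BP is wanted, stratify on it.
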